### Study design

This study has a multicenter, randomized, controlled, single-blind design. Patients will be randomized to two different arms: (1) intervention group (individualized BP lowering), with an individualized target for BP lowering during the first week of hospitalization; and (2) control group (guideline-recommended BP lowering), with a fixed target recommended by the guideline for BP lowering during the first week of hospitalization. The participants are blind to the grouping results; the researchers are informed of the grouping results because they have to follow a specified strategy of BP management. Figure 1 shows a flowchart of the study design. Recommendations for Interventional Trials (SPIRIT) Figure are outlined in Additional file 1.

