### Trial interventions

In patients who are assigned to receive individualized regimen to lower BP (individualized BP-lowering group), antihypertensive treatments are to be initiated to reduce SBP to a range of 130–180 mmHg and by 10–15% from the admission level within 2 h after randomization. SBP in the individualized BP-lowering group is to be maintained around the target level for one week with or without the use of hypertensive agents. In participants who were assigned to receive guideline-recommended treatment [13, 14] (guideline-recommended BP-lowering group), antihypertensive agents are to be administered if the SBP was > 200 mmHg in acute ischemic stroke (AIS) or the SBP was > 180 mmHg in intracerebral hemorrhage (ICH). The goal is to maintain the SBP < 200 mmHg in ischemic stroke and < 180 mmHg in ICH for one week with or without the use of hypertensive agents. Table 1 presents the detailed management of BP in the first week after randomization.

**Table 1 Tab1:** Management of BP during the first week after randomization

SBP level	Approaches
*Individualized BP-lowering group*	
Above the range^a^	Increase the dose of AHD or use other stronger AHDs
In the range^a^	Maintain the regimen
Below the range^a^ and > 100 mmHg	Reduce the dose of AHD or withdraw AHD
< 100 mmHg	Use vasopressor agents
*Guideline-recommended BP lowering-group*	
> 200 mmHg in AIS > 180 mmHg in ICH	Increase the dose of AHD or use other stronger AHDs
< 200 and > 100 mmHg in AIS < 180 and > 100 mmHg in ICH	Use the least dose of AHD to keep SBP not > 200 mmHg in AIS, 180 mmHg in ICH
< 100 mmHg	Use vasopressor agents

^a^10–15% reduction from admission level and in the range of 130–180 mmHg

*AHD* antihypertensive drug, *AIS* Acute ischemic stroke, *BP* blood pressure, *ICH* intracerebral hemorrhage, *SBP* systolic blood pressure

The selection of antihypertensive agents is based on the local availability; no specific agent is stipulated (both intravenous and oral agents can be used). Patients who take antihypertensive agents before stroke continue to take the same antihypertensive medication (same drug with same dosage). The rest of the medical care for stroke is based on the guideline [15, 16]. The management of BP after the first week of hospitalization adheres to the guideline as well.

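### The rule to keep home antihypertensives at an unchanged dose contradicts Table 1 for individualized-arm patients below range, and the treated week is dated from hospitalization in some places and from randomization in others

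*Protocol article*

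**What the plan says.** **Home drugs.** In the paragraph after Table 1, Trial interventions states: "Patients who take antihypertensive agents before stroke continue to take the same antihypertensive medication (same drug with same dosage". The sentence names no arm, no SBP level and no exception.

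Table 1 in the same section sets actions by SBP level:

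- Individualized arm, below range and above 100 mmHg: "Reduce the dose of AHD or withdraw AHD".
- Either arm, below 100 mmHg: "Use vasopressor agents". Nothing is said about antihypertensive drugs (AHD) in this row.
- Guideline arm, between 100 mmHg and the threshold: "Use the least dose of AHD to keep SBP not" above 200 mmHg in ischemic stroke or 180 mmHg in hemorrhage.

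The table's abbreviation list expands AHD only as antihypertensive drug. It does not separate home drugs from drugs added in the trial.

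**Clock.** Study design describes the intervention arm "with an individualized target for BP lowering during the first week of hospitalization" and uses the same period for the control arm. The last sentence of Trial interventions reads: "The management of BP after the first week of hospitalization adheres to the guideline as well". Table 1, however, is titled "Management of BP during the first week after randomization". Its lead-in sentence, the 2 h limit for reaching the target, and the first 24 h of readings in Blood pressure monitoring also start at randomization. Individualized-arm SBP "is to be maintained around the target level for one week".

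**The concern.** Two stated instructions collide for a foreseeable patient: one who took antihypertensives before the stroke, was assigned to the individualized arm, and falls below the target range with no trial-added drug to cut. The protocol does not say which instruction prevails. If a site follows the home-drug sentence, the patient stays on treatment that Table 1 would reduce. The Discussion notes that blood pressure can fall without medication in acute stroke and that a fall may reduce brain perfusion. It also reports that, in the sponsor's retrospective one-hospital study, intensive care mortality was higher when SBP fell by more than 15%, and it names this result as part of the basis for the design.

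The clock matters because the last sentence of Trial interventions is operative: it moves the patient from the assigned regimen to guideline management. If that switch is timed from admission, a patient randomized later receives less than the assigned week.

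**Working it through.** **1. Which situations contradict each other?** The home-drug sentence (keep drug and dose) is set against each row of Table 1.

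| Situation of a prior user | Table 1 action | Compatible with an unchanged home dose? |
|---|---|---|
| Individualized, above range | Increase dose or use stronger drugs | Yes, by adding a drug |
| Individualized, in range | Maintain | Yes |
| Individualized, below range, added drug in use | Reduce or withdraw | Yes, by cutting the added drug first |
| Individualized, below range, home drug only | Reduce or withdraw | **No** |
| Either arm, below 100 mmHg | Vasopressor | Not contradictory, because the row is silent on AHD; read together, the rules allow a vasopressor beside a full home dose |
| Guideline arm, above threshold | Increase dose or use stronger drugs | Yes, by adding a drug |
| Guideline arm, 100 mmHg to threshold | Least dose | In tension if the home dose exceeds the least dose (see the objection) |

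**2. How deep a fall does below range mean?** Inputs: the target is a 10–15% reduction from admission and lies within 130–180 mmHg (Table 1 footnote); entry SBP is 150–210 mmHg (Study population). I assume that admission SBP, A, lies in the entry window.

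Lower limit = max(130, 0.85 × A). Upper limit = min(180, 0.90 × A). The 15% limit governs once 0.85 × A ≥ 130, that is, A ≥ 130/0.85 = 152.9.

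| Admission SBP | Target range | Below range means a fall of more than |
|---|---|---|
| 150 | 130–135 (127.5 raised to 130) | 20/150 = 13.3% |
| 152 | 130–136.8 (129.2 raised to 130) | 22/152 = 14.5% |
| 180 | 153–162 | 27/180 = 15% |
| 200 | 170–180 | 30/200 = 15% |
| 210 | 178.5–180 (189 cut to 180) | 31.5/210 = 15% |

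For every admission SBP from 153 to 210 mmHg, the row that orders reduction or withdrawal begins at a fall of just over 15%. It can apply at pressures far from hypotension: up to 130 mmHg for A = 150 and up to 178.5 mmHg for A = 210.

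The 100 mmHg row corresponds to a fall of more than 50/150 = 33.3% from 150 mmHg and more than 110/210 = 52.4% from 210 mmHg. These figures locate the row; they do not measure any effect of home drugs.

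Patients whose initial SBP was below 150 mmHg and who qualified on rechecking may have an admission SBP outside this window. The depth figures do not cover them, but the contradiction in step 1 does not depend on those figures.

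**3. How far apart are the two clocks?** The week by hospitalization ends at admission + 7 days. The week by randomization ends at randomization + 7 days. The difference is (randomization − admission), the delay d.

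- d = 0 for a patient randomized at admission: no difference.
- d > 0 is allowed. Study population lets the regimen start up to 72 h after onset and lets patients first below 150 mmHg be randomized on rechecking within that window.
- If admission is not before onset, d cannot exceed 72 h, so at least 7 − 3 = 4 days of the assigned week remain. This is a limit, not an estimate. The protocol gives no distribution of d.

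**The case against.** **An ordinary reading reconciles much of the text.** The home-drug sentence sits in a paragraph on choice of agents and can be taken as the starting background. Table 1 is introduced as the detailed management and so looks like the specific rule. The same section says SBP may be kept at target with or without drugs, so being on no drug is already foreseen. The published article is also a condensation. This stands in part: many clinicians would let Table 1 prevail. But the home-drug sentence specifies the same dosage without condition, and nothing ranks the two rules. Reading Table 1 as covering only added drugs leaves no action for a below-range patient on home drugs alone. These are two stated rules that conflict, not detail left out.

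**A reader might infer that Table 1 is contradicted in both arms and at every low pressure.** The text does not support that. The row below 100 mmHg says nothing about AHD, so it leaves a safety gap and not a contradiction.

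**A reader might also infer that the least-dose row should govern the home drugs of controls below threshold.** The two rules are in tension there, but cutting home treatment in those controls would change the comparator during recruitment. Controls have no SBP floor other than 100 mmHg, so a fall above 15% is within their protocol. Whether they keep home drugs is a design choice for the sponsor.

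**The mortality result proves no harm.** That is correct. It is a retrospective association from one hospital, significant in ischemic stroke and not in hemorrhage. It shows only that the unchanged dose works against the trial's own rationale.

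**The clock point is editorial.** Most operative text runs from randomization, and Table 2 heads its columns by day of enrollment. That limits the point's size. The last sentence of Trial interventions is nonetheless an instruction to switch management, and it uses the other clock.

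**Conclusion.** Both parts hold in limited form.

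1. In the individualized arm, the unconditional home-drug rule contradicts Table 1 for a prior user who is below range with no added drug left to reduce. For admission SBP of 153–210 mmHg this is a fall of more than 15%; at 150 mmHg it is a fall of more than 13.3%. Below 100 mmHg, in either arm, the text permits an unsafe combination without directly contradicting itself.
2. Study design and the last sentence of Trial interventions date the treated week differently from Table 1, its lead-in and Blood pressure monitoring. The assigned week is shortened by the admission-to-randomization delay, which is zero for patients randomized at admission and otherwise not given.

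The depth figures assume that admission SBP lies within the entry window. The number of patients affected cannot be determined, and neither can the direction of any bias. The documents do not support a claim that home drugs cause harm here, that a particular share of the week is lost, or that the treatment comparison is biased. Severity is minor to moderate: the part on home drugs bears on safety, and the clock is the smaller part.

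**What to change.** Replace the home-drug sentence with:

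*Patients taking antihypertensive agents before stroke continue the same drug and dose, except that in the individualized arm, when SBP is below range, any added drug is reduced first and home drugs are then reduced or withdrawn as in Table 1; in either arm home drugs are withheld while SBP is < 100 mmHg.*

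Do not extend the least-dose rule to home drugs of controls below threshold as part of this amendment.

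In Study design (both arms) and in the last sentence of Trial interventions, change the first week *of hospitalization* to the first week *after randomization*.

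The cost is one amendment through the route in Protocol amendments, with no added visits, patients, data items or changes to outcomes. Trial status says that recruitment has started, so the change applies prospectively. A few prior users may therefore be managed differently before and after it, which is a small downside.

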### Study procedures

Table 2 presents all the variables measured at each time point of the study. At the time point of baseline screening, demographics, subtypes of stroke, medical history (e.g. AIS, ICH, coronary event, diabetes mellitus, and hypertension), physical examination, clinical scores (NIHSS, GCS, Barthel index, mRS), and vital signs are recorded. On day 1 and day 7, routine laboratory tests for stroke patients are assessed, including blood routine, liver and renal function test, serum lipid, fasting glucose, urine routine, and electrocardiography. Co-morbidities on the day of screening and hospital discharge are recorded. Clinical scores on day 7, the day of hospital discharge, and day 90 are collected. During the whole hospitalization, BP, vital signs, and adverse events (AEs) are monitored, and concomitant treatments are documented.

**Table 2 Tab2:** Timing and content of study assessments

Items	Day of enrollment									
	Screening	1	2	3	4	5	6	7	HD	90
Written informed consent	●									
Inclusion and exclusion criteria	●									
Demographics	●									
Medical history	●									
Physical examination	●							●	●	
BP monitoring	●	●	●	●	●	●	●	●	●	
Laboratory tests		●						●		
NIHSS and GCS	●								●	
Barthel index and mRS	●								●	●
Vital signs monitoring	●	●	●	●	●	●	●	●	●	
Co-morbidities	●								●	
AEs		●	●	●	●	●	●	●	●	
Use of antihypertensive agents		●	●	●	●	●	●	●	●	
Concomitant therapies		●	●	●	●	●	●	●	●	

*HD* hospital discharge, *BP* blood pressure, *GCS* Glasgow Coma Scale, *NIHSS* National Institute of Health stroke scale, *mRS* modified Rankin Scale, *AE* adverse event

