## Background

Elevated blood pressure (BP) is one of the most common clinical manifestations in acute stroke; 70–84% [1–3] of stroke patients have a systolic blood pressure (SBP) > 140 mmHg on admission. Despite efforts by a few multicenter studies, the optimum management of BP in acute stroke is still an ongoing dilemma. The ACCESS study and CHHIPS study indicated that modest BP reduction brought down the mortality and the number of vascular events [4], whereas the SCAST study suggested that a careful BP-lowering treatment was associated with a higher risk of poor outcome. The results from the COSSACS study, CATIS study, ATACH-2 study, and INTERACT2 study are neutral: intensive lowering of BP did not reduce the mortality or severe disability significantly [5–8].

However, none of the above studies were targeted at patients with severe stroke. Acute severe strokes account for 13–24% of all strokes [9, 10] and are associated with cerebral hernia, acute cardiac failure [11], systemic complications [12], and death. Given the paucity, we initiated a multicenter randomized controlled trial (RCT) called CHASE, dedicated to test whether individualized antihypertensive treatment would lower the mortality and major disability in patients with severe stroke.

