## Methods

### Study objectives

The study aims at assessing the effect of individualized BP-lowering regimens vs guideline-recommended BP-lowering regimens on mortality and morbidity in patients with acute severe stroke.

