### Outcome measurement

The primary outcome measurement is the proportion of participants with a poor outcome at day 90 of enrollment. Poor outcome is defined as major disability (mRS ≥ 3, unable to live independently) or all-cause death. The proportion of participants with a poor outcome at hospital discharge is the key secondary outcome. Other secondary outcomes are the disability (evaluated by NIHSS, GCS, and Barthel index) at hospital discharge and the ability of activities of daily living at day 90 of enrollment evaluated by Barthel index. Outcomes are assessed independently by trained research assistants who are blind to the grouping results and clinical data. The 90-day outcomes are evaluated via telephone interviews at day 90 of enrollment (a delay of up to three days is acceptable). In cases when the patient is incapable to complete the interview, the first choice for a proxy is the spouse/live-in companion.

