## Discussion

A few multicenter, randomized studies have been carried out to search for the ideal BP range for patients with acute stroke; however, none of them aimed at severe stroke, which has a much higher rate of mortality and disability. No clinical evidence can be used to guide the BP management in critical care for those stroke patients with an initial presentation of severe neurological deficits. Our study aims to test the superiority of individualized BP lowering compared to guideline-recommended BP lowering in improving three-month outcome. Our study will provide the first evidence on the optimum BP-lowering target for patients with acute severe stroke.

Factors that contribute to raised BP in acute stroke are multifaceted, such as history of hypertension, stroke severity, pressure response to hospital admission, infarct area related to BP adjustment, and increased intracranial pressure [19]. Raised BP later falls into the following types: without antihypertensive medications BP declines spontaneously; with antihypertensive medications BP does not decline, declines modestly (10–15% from baseline), or intensively (≥ 20% from baseline value) [20]. Elevated BP raises the risk of cerebral edema, hemorrhagic transformation of the infarct [21], hematoma expansion [22], cardiac complications, and renal insufficiency. On the other hand, a decrease in BP might reduce the blood perfusion of the brain and aggravate the cerebral ischemic injury, especially in large territorial ischemia [23]. One clinical study indicated that both large increase and reduction in BP (> 20 mmHg) were associated with a higher risk of early neurological deterioration, increased infarct volume, and poorer outcome at three months [24]. Therefore, a proper management of BP is essential for stroke patients.

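### Adverse-event recording stops at hospital discharge while benefit is judged at day 90, so non-fatal events after discharge and causes of later death have no scheduled capture

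*Protocol article*

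**What the plan says.** In the protocol article, Study procedures gives the adverse-event window in words: "During the whole hospitalization, BP, vital signs, and adverse events (AEs) are monitored, and concomitant treatments are documented". The same section introduces its schedule as complete: "Table 2 presents all the variables measured at each time point of the study". In Table 2 the adverse-event row is marked on each of days 1 to 7 and at hospital discharge, and is empty at day 90. The only row marked at day 90 is "Barthel index and mRS". Co-morbidities are recorded at screening and discharge only.

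Outcome measurement sets the primary outcome at day 90 as mRS of 3 or more, or death from any cause. It also describes the contact: "The 90-day outcomes are evaluated via telephone interviews at day 90 of enrollment". Assessors are blinded, a proxy may answer, and the call may be up to three days late.

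Study objectives states the aim as the effect of the two regimens "on mortality and morbidity in patients with acute severe stroke". Under Trial interventions, the assigned blood pressure targets apply for one week, after which both arms follow the guideline.

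**The concern.** Benefit is judged over 90 days, but adverse events are recorded only up to a day that differs from patient to patient. The protocol itself gives reasons to care about events beyond disability. The Background recalls earlier trials in which "modest BP reduction brought down the mortality and the number of vascular events". The Discussion lists "cardiac complications, and renal insufficiency" among the risks of elevated pressure, and reduced brain perfusion as a risk of lowering it.

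The mRS measures net disability. It cannot separate a second stroke from poor recovery after the first, and it can miss a cardiac or renal event that leaves the score unchanged. If the arms differ on mRS at day 90, the trial will have little information on which later events explain or offset that difference. If they do not differ, it cannot say whether non-fatal events after discharge did.

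**Working it through.** The protocol gives no figure to reproduce here, so the main check sets its statements side by side.

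| Item | In hospital | Discharge to day 90 |
|---|---|---|
| Adverse events (text and Table 2) | Recorded; marked on days 1 to 7 and at discharge | Not scheduled |
| Co-morbidities (text and Table 2) | Screening and discharge | Not scheduled |
| Death from any cause (Outcome measurement) | Captured | Captured in the primary outcome |
| Cause of death | No separate item listed | No item listed |
| Disability (mRS, Barthel) | Screening and discharge | Day 90 |
| Non-fatal stroke, cardiac or renal event, rehospitalization | The events, through adverse events | Only indirectly, if mRS or Barthel changes |

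**Do text and table agree?** On adverse events, yes: both stop at discharge. On scores they do not quite match. The text says "Clinical scores on day 7, the day of hospital discharge, and day 90 are collected", with clinical scores having been listed as NIHSS, GCS, Barthel and mRS, whereas Table 2 marks no scores on day 7 and no NIHSS or GCS at day 90. On either reading, day 90 holds scores only, not events.

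**Does another section extend the window?** Data quality mentions checking serious adverse events that have been reported, but gives no reporting period. Table 2 lists no contact between discharge and day 90.

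**How much of follow-up is observed?** For a stay of L days from enrollment, the share under adverse-event recording is L/90. The protocol does not give L, so these values are assumptions:

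- L = 7: 7/90 = 8%, leaving 83 days unrecorded
- L = 10: 10/90 = 11%, leaving 80 days
- L = 14: 14/90 = 16%, leaving 76 days
- L = 21: 21/90 = 23%, leaving 69 days
- L = 30: 30/90 = 33%, leaving 60 days

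These are shares of calendar time, not of events. Events are likely to be concentrated early, so the share of events captured would probably be higher.

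**Would an in-hospital comparison between arms be distorted?** With the same constant daily rate r in both arms, expected counts per patient are r × L1 and r × L2, and their ratio is L1/L2. The ratio is 1 if mean stays are equal and departs from 1 only if they differ. The protocol gives no stay by arm, so no size can be attached.

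**The case against.** The strongest defence is that the window fits the intervention. The assigned regimens last one week, adverse events are scheduled on every day of that week and then to discharge, and laboratory tests including renal function and electrocardiography are planned on days 1 and 7. For a one-week strategy this is a defensible choice. It stands as a limit on severity, and the treatment week is covered for anyone still in hospital. It does not remove the mismatch, because the trial expects one week of treatment to change the outcome at day 90.

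Second, the protocol never promises 90-day rates of recurrent stroke, cardiac or renal events. The Background narrows the aim to death and major disability, the vascular-event result belongs to earlier trials, and the Discussion names cardiac and renal problems as risks, not endpoints. This also stands: no stated objective is broken.

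Third, an article condenses a fuller protocol. That does not dispose of the point, because the schedule is stated outright and the table is presented as complete.

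A reader might go further and infer that events after discharge are lost altogether, or that safety will be compared over unequal observation times. The documents do not support either. Deaths and disabling events reach the primary outcome. The Statistical and analytical plan states between-arm comparisons only for the primary and secondary outcomes, and no safety endpoint is defined. A reader might also suppose that unblinded staff influence stay by deciding discharge. The Study design says that researchers know the allocation, but nothing says who decides discharge or that stay differs by arm.

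**Conclusion.** The point holds in a limited form. Recording of adverse events ends at a patient-specific discharge day, while the primary outcome runs to day 90 and the day-90 column marks only two scales. What goes uncaptured is the identity of non-fatal events after discharge, the non-disabling events entirely, rehospitalizations, and the cause of later deaths.

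The size cannot be fixed from the documents. The 8% to 33% of follow-up time rests on assumed stays of 7 to 30 days. Any between-arm comparison confined to the stay would have unequal observation times if stay differed by arm, but none is stated and no stay data are given. This is a cheap improvement of low severity and does not undermine the primary analysis.

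**What to change.** - Add an adverse-event mark at day 90 in Table 2, and make the Study procedures text match.
- At the planned call, after mRS and Barthel have been scored, ask closed questions on recurrent stroke, cardiac event, kidney failure and rehospitalization, each with its date, and on the date and cause of any death. Asking them last keeps the answers from influencing the blinded scoring.
- Report patients with at least one event per arm, as randomized, in two fixed windows: randomization to day 7 and randomization to day 90. Give the risk difference with a 95% confidence interval. Event dates allow both windows to be filled for patients discharged before day 7.

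The cost is a few questions in an existing call, one case report form page and a short amendment, with no extra visit or staff. There are two downsides. Events after discharge come from the patient or a proxy and are less certain than in-hospital records, so they should be labelled as such. Trial status says that recruitment has started and follow-up is under way, so patients already past day 90 will lack these data or need re-contact; the report should state how many patients were asked.
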